User lifestyle feedback	Comparison of changes in user lifestyle (at baseline and after 6 months) through the questionnaires: EQ-5D-5 L, IPAQ for physical activity, and SF-36	• Smoking cessation rate • Mobile app usage	• Clinical	App influence on users physical activity levels
Physical activity	Total time (min) of activity per user, retrieved by GoogleFit	• Smoking cessation rate • Mobile app usage	• Public • Clinical	App influence on users physical activity levels

*EQ-5D-5 L* EuroQol 5-dimension 5-level questionnaire, *IPAQ* International Physical Activity Questionnaire, *SF-36* Short Form 36-item Health Survey

Although they are not necessary to the assessment of the primary and secondary outcomes, the metrics described in Table 3 will also be retrieved and analyzed because they are considered relevant and potentially useful.

**Table 3 Tab3:** Description of additional metrics to be measured in the study

Metric	Calculation	Pilot
User reliability	Comparison of the abstinence self-report at 2-week intervals with the measurements of the CO-oximeter	Clinical
QALY (financial aspects)	Healthcare resource utilization and cost analysis (cost of devices used, pharmacological treatment and time spent for various purposes)	Clinical
Precision of the recommender system	Messages sent and rated more than four stars / total number of rated messages	Public Clinical
Smoke-free period	Time range between quitting date and the last smoke-free report	Clinical

*CO* carbon monoxide, *QALY* quality-adjusted life year

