### Statistical analysis

In the clinical pilot, patients will be classified as either smokers or non-smokers according to their positive or negative values in the urine test and the expired CO tests (PiCO values between 0 and 6 will be considered non-smokers) at each follow-up visit. In case of discrepancy between tests, we will consider the patient as a smoker. We will perform repeated analysis of variance (ANOVA), and provide *p* values, to compare the number of non-smokers in the intervention versus control group at 2 months, 4 months and 6 months of their quitting day.

In the public pilot, users will be considered to be non-smokers according to their self-reported answer to the question: “Are you still resisting the temptation or have you smoked? Please, be honest.” We will perform repeated ANOVA, and provide *p* values, to compare the number of non-smokers in the intervention versus control group every 2 weeks.

For secondary outcomes, the numerical variables (user engagement at aggregated level, user mobile app usage, user quitting attempt, user app behavior, and user lifestyle feedback EuroQoL 5 dimensions 5 levels questionnaire (EQ-5D-5 L) and Short Form 36-item Health Survey (SF-36), and physical activity) will be assessed with *T* tests and variance ANOVA tests. Categorical variables (user engagement at individual level, user satisfaction with messages, user message ratings, and lifestyle answers to the International Physical Activity Questionnaire (IPAQ)) will be assessed with chi-square tests. In addition, we intend to study the combination of all metrics with a linear regression analysis, and the Kaplan-Meier method to analyze the overall survival rate (non-smokers). All tests will be two-tailed and with a significance level set at 0.05. All analyses will be done according the intention-to-treat principle, and using the SPSS software version 25. Missing data will be calculated with the last observation carried forward.

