**Fig. 3 Fig3:**
[figure not shown]
Screenshots of the app (English and Mandarin versions) showing different sections

A nurse will provide patients with instructions for downloading and using the app. Questions related to the patient’s basic demographic information and an extended profile (including social influences, plan of action, skills, attitudes, and self-efficacy with regard to smoking) will be assessed in the app.

The data obtained from the database will be analyzed in a comma-separated value (CSV) format using SPSS software.

Users’ physical activity data will be collected using their mobile phones. The mobile app will use GoogleFit [40] to track daily physical activity. These data will be available to users through the GoogleFit app but not displayed within the 3M4Chan app, as it will be utilized for research purposes only.

Patients will be followed up after 60, 120, and 180 days of their initial consultation with a variance margin of 5 days. In the initial consultation, the patient will be assessed in the smoking cessation unit after they have been referred from either the pneumology unit or another clinical department. Smoking-related symptoms, treatment adherence, daily cigarette use, and possible adverse events will be discussed and exhaled carbon monoxide, urinary cotinine, and other clinical information, such as weight and height, will be assessed. Quality of life (EQ-5D-5 L, IPAQ, and SF-36) questionnaires will also be collected. The patient will be instructed on relaxation techniques and on tips to avoid smoking.

During the second consultation, physicians will gather patient information on smoking-related symptoms, treatment adherence, daily cigarette use, possible adverse events, exhaled carbon monoxide and urinary cotinine levels, and other clinical information. Coaching for relapse prevention will be performed.

At the third consultation, information about smoking-related symptoms, treatment adherence, possible adverse events, exhaled carbon monoxide and urinary cotinine levels, and other clinical information will again be collected. New relaxation techniques will be explained if the previously taught techniques have not been effective. Techniques for relapse prevention will be reviewed. It will also be collected the users’ physical and psychological health state, their exhaled carbon monoxide levels, the results from a urinary cotinine test, and will be asked clinical information such as weight and height.

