At the fourth consultation, physicians will collect information about smoking-related symptoms, treatment adherence, and possible adverse events. Techniques for avoiding the risk of relapse are reinforced. Data about blood pressure, weight, height, and quality of life (using EQ-5D-5 L, IPAQ, and SF-36 questionnaires as well as a questionnaire assessing the satisfaction about the motivational messages received through the 3M4Chan app) will also be collected. All input clinical data will be checked for correctness by two healthcare professionals to ensure quality.

The public pilot will use the same mobile app as the clinical pilot. No additional materials will be used.

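### Baseline EQ-5D-5L, SF-36 and IPAQ values are collected in the clinical pilot, but the named tests do not use them as a covariate, so an intervention-versus-control comparison of these secondary measures is valid but less efficient than it could be

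*Protocol article*

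**What the plan says.** In Table 2 (Measures section) the lifestyle metric is a "Comparison of changes in user lifestyle (at baseline and after 6 months) through the questionnaires: EQ-5D-5 L, IPAQ for physical activity, and SF-36". It applies to the clinical pilot only. The Comparisons column sets it against the smoking cessation rate and mobile app usage.

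The Materials section has the questionnaires completed twice. At the initial consultation, "Quality of life (EQ-5D-5 L, IPAQ, and SF-36) questionnaires will also be collected". At the fourth consultation the data again include "quality of life (using EQ-5D-5 L, IPAQ, and SF-36 questionnaires".

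The Statistical analysis section splits the metric by variable type. The numerical group includes "user lifestyle feedback EuroQoL 5 dimensions 5 levels questionnaire (EQ-5D-5 L) and Short Form 36-item Health Survey (SF-36" and goes to t "tests and variance ANOVA tests". For the categorical group, the section states that "lifestyle answers to the International Physical Activity Questionnaire (IPAQ)) will be assessed with chi-square tests". It does not say whether the t tests are paired or independent, whether the ANOVA for these scores uses repeated measures, or which table the chi-square is run on. It adds that "we intend to study the combination of all metrics with a linear regression analysis", without naming an outcome or covariates.

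**The concern.** The metric is a within-patient change, and each patient's baseline value is on file. Chi-square has no place for a baseline value unless each patient is first reduced to one change category, a step the article does not describe. The t test and ANOVA can use baseline by working on the difference, but neither is given baseline as a covariate. When the follow-up value is correlated with baseline, leaving it out as a covariate discards information already collected.

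What is at stake is precision. The clinical pilot has 100 patients and was sized for smoking cessation, not for these questionnaires. A moderate difference in quality of life or activity could be missed although the data to detect it more reliably are available.

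**Working it through.** **The plan's own figure.** The article gives no sample size, SD, correlation or power for the questionnaires. Its only relevant figure is the clinical pilot's 45 per group (0.2 versus 0.5, two-sided alpha 0.05, power 0.80).

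- Uncorrected: n = [1.96·√(2·0.35·0.65) + 0.8416·√(0.2·0.8 + 0.5·0.5)]² / 0.3² = 38.5, so 39.
- Continuity-corrected: (38.48/4)·[1 + √(1 + 4/(38.48·0.3))]² = 44.9, so 45.

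The stated 45 is reproduced. It concerns the primary outcome only.

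**Scores (EQ-5D-5L, SF-36), intervention versus control.** Inputs: 50 per arm (Table 1) and two-sided alpha 0.05 (Statistical analysis). Assumptions: SD 1 at both visits, effect 0.5 SD, within-patient correlation rho of 0.3, 0.5 or 0.7.

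- Month 6 only: variance 1
- Change from baseline: variance 2(1 − rho)
- ANCOVA: variance 1 − rho²
- Ratio of ANCOVA to change: (1 − rho²)/[2(1 − rho)] = (1 + rho)/2
- Power = Φ(0.5/[SD·√(2/50)] − 1.96) = Φ(2.5/SD − 1.96)

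Example at rho 0.3: change SD = √1.4 = 1.183, so Φ(2.113 − 1.96) = 56.1%. ANCOVA SD = √0.91 = 0.954, so Φ(2.621 − 1.96) = 74.6%.

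| rho | Variance ratio, ANCOVA/change | Month 6 only | Change | ANCOVA | ANCOVA minus change |
|---|---|---|---|---|---|
| 0.3 | 0.65 | 70.5% | 56.1% | 74.6% | 18.5 points |
| 0.5 | 0.75 | 70.5% | 70.5% | 82.3% | 11.8 points |
| 0.7 | 0.85 | 70.5% | 89.8% | 93.8% | 4.0 points |

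ANCOVA is ahead of both alternatives in every row. With 45 per arm, change against ANCOVA is 51.8% v 70.1%, 66.0% v 78.2% and 86.5% v 91.3%. With an assumed effect of 0.3 SD and 50 per arm it is 24.4% v 34.9%, 32.3% v 41.0% and 49.1% v 55.6%. The direction does not change.

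**IPAQ, intervention versus control at month 6.** Simulation: three categories cut from a correlated normal variable, 50 per arm, 3,000 runs per setting, assumed latent shift 0.5 SD. The baseline-adjusted comparator is a linear analysis of the category score, standing in for an ordinal model.

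| rho | Chi-square by arm, null rejection | Chi-square by arm, power | Baseline-adjusted score, power | Difference |
|---|---|---|---|---|
| 0.3 | 5.4% | 50.2% | 62.0% | 11.8 points |
| 0.5 | 4.7% | 49.6% | 68.1% | 18.5 points |
| 0.7 | 4.8% | 48.1% | 77.4% | 29.3 points |

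The by-arm chi-square holds its 5% level and only loses power. Part of the loss comes from ignoring category order rather than baseline. The simulation does not separate the two.

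**IPAQ, baseline against month 6 in the same patients.** If the chi-square were run on answer by visit, each patient would count twice as if independent. With no true change, the same simulation rejects in 3.1%, 2.1% and 1.3% of runs at rho 0.3, 0.5 and 0.7, against a nominal 5%. This is the one reading under which the test is invalid, and the error is conservative.

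**The case against.** The strongest reply is that the article states no error. A change-score t test is valid in a randomised comparison. So is a chi-square by arm, or a chi-square on one change category per patient. Table 2's word for the metric is change, and it covers IPAQ as much as the scores. The paired or unpaired form and the covariates are details often left to a statistical analysis plan, which is not shown. Table 2 compares lifestyle feedback with cessation and app usage, not with randomised group. For quitters against non-quitters, ANCOVA and change scores estimate different quantities, so ANCOVA is not automatically the better choice.

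Most of this stands, and it sets the limits of the point. Three stronger readings that a reader might infer are not supported:

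- *Pairing and baseline are ignored for the scores.* A change score is month 6 minus baseline in the same patient and uses both. At rho 0.7 it clearly beats a month-6-only test (89.8% against 70.5%). The accurate criticism is only that baseline is not a covariate.
- *The IPAQ standard error is wrong.* That holds only for answer by visit, and the article does not say that this table is intended.
- *The activity objective could be lost for this reason alone.* Table 2 also measures activity by GoogleFit minutes, in both pilots.

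What the reply does not remove is that the section does name the tests, and none of them adjusts for baseline. The linear regression on all metrics cannot be counted as that adjustment, since it has no stated outcome or covariates.

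**Conclusion.** The point holds as one of efficiency. For an intervention-versus-control comparison in the clinical pilot, the named tests are valid but less precise than baseline-adjusted ones. The cost is about 4 to 19 power points for the scores, if they are analysed as change, and about 12 to 29 for IPAQ, if chi-square is run on month-6 answers by arm. The variance ratio (1+rho)/2 is exact for equal SDs at the two visits. The correlations, the 0.5 SD effects and the IPAQ categories are assumptions, because the article gives none, so the true loss cannot be fixed from it. The by-visit chi-square is a conditional risk, not a stated error.

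The matter is minor: secondary outcomes, one pilot, no effect on the primary analysis. It does not extend to comparisons of quitters with non-quitters or by app usage.

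**What to change.** In the Statistical analysis section, for the comparison of the randomised groups in the clinical pilot:

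- Analyse month-6 EQ-5D-5L and SF-36 scores by ANCOVA, with group as factor and the baseline score as covariate.
- Analyse the month-6 IPAQ category by ordinal logistic regression on group, with the baseline category as covariate.
- For any within-patient IPAQ comparison of baseline with month 6, use McNemar (two categories) or Stuart-Maxwell (three or more) in place of chi-square.

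Limit the new wording to these comparisons. Do not carry ANCOVA over by default to the groupings by cessation or app usage in Table 2.

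The cost is a few sentences. No new data, visits or patients are needed, and the methods are standard in ordinary statistical software.

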### Sample size and power calculations

Calculations regarding the needed number of participants to measure the primary outcome – smoking cessation rates – have been done to ensure the statistical significance of the results.

For the clinical pilot, accepting an alpha risk of 0.05 and a beta risk of 0.2 in a two-sided test, 45 subjects will be necessary in both the first group and second groups in order to find a statistically significant proportion difference, which is expected to be 0.2 and 0.5 in the first and second groups, respectively.

For the public pilot, accepting an alpha risk of 0.05 and a beta risk of 0.2 in a two-sided test, 489 subjects are necessary in first group and 489 in the second to find as statistically significant a proportion difference, expected to be of 0.07 in group 1 and 0.14 in group 2.

A dropout rate of 15 and 20% is anticipated for the clinical and public pilot, respectively. Although other studies using computer-tailored interventions have reported higher dropout rates, this study will consider participants who do not return for the consultation at month 6 to be failure cases. Consequently, the anticipated dropout rates include only those who withdraw for reasons other than relapse.

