### Problems anticipated

The dropout rate among participants is one of the main challenges we anticipate for this study. Patients might dropout by ceasing to share EHR data, by terminating their use of the app, or by becoming unresponsive to follow-ups over the course of the trial.

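### Smoking status has two conflicting missing-data rules: last observation carried forward in the analysis section, non-return at month 6 counted as failure in the sample-size section

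*Protocol article*

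**What the plan says.** Statistical analysis section: "Missing data will be calculated with the last observation carried forward". The sentence follows the primary and secondary analyses and names no variable to which it does not apply. The same section says "All analyses will be done according the intention-to-treat principle", so randomised participants without an outcome have to be given one. It also classifies cautiously elsewhere: a clinical-pilot patient whose urine and breath tests disagree counts as a smoker.

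Sample size and power calculations section: "A dropout rate of 15 and 20% is anticipated for the clinical and public pilot, respectively". The article concedes that comparable studies lost more, and explains its lower figures thus: "this study will consider participants who do not return for the consultation at month 6 to be failure cases". From this it concludes that "the anticipated dropout rates include only those who withdraw for reasons other than relapse".

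Problems anticipated section: participants may drop out in several ways, among them "by terminating their use of the app, or by becoming unresponsive to follow-ups over the course of the trial".

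Smoking status is assessed at 60, 120 and 180 days, and in the public pilot it is compared every two weeks from a self-reported answer. A missing month-6 value will therefore often have an earlier value available to carry forward.

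**The concern.** The two rules disagree about one kind of participant: someone last recorded as a non-smoker who has no month-6 assessment. Carry-forward makes that person abstinent, and the failure rule makes the same person a smoker. Nothing in the article says which rule governs the primary outcome.

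This kind of participant is unlikely to be rare. The article expects people to go silent, and someone who relapses has a plain reason to stop answering. In the public pilot the carried value would be an unverified in-app answer, so a user who reports abstinence early and then removes the app could be counted as abstinent at six months.

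Two things are at stake. The reported abstinence rates depend on the rule chosen. So does the comparison between arms, if the arms differ in how many people go silent or in their status when they do. With both rules in print, the choice could also be made after the data are seen.

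**Working it through.** **1. The two rules side by side (month 6, no assessment)**

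| Last recorded status | Carry-forward | Failure rule |
|---|---|---|
| Smoker | smoker | smoker |
| Non-smoker | non-smoker | smoker |

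Only the second row conflicts.

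**2. The plan's own figure.** Clinical pilot: "accepting an alpha risk of 0.05 and a beta risk of 0.2 in a two-sided test, 45 subjects will be necessary" per group, for a proportion "which is expected to be 0.2 and 0.5 in the first and second groups, respectively". The pooled two-proportion formula gives 38.5, so 39 per group; with continuity correction it gives 44.9, so 45. The stated figure is reproduced. The formula takes no missing-data rule as an input. The public pilot's 489 does not follow from its stated inputs (300 pooled, 328 with continuity correction; 375 and 410 after allowing for 20% dropout). That is a separate matter, and the work below uses the planned enrolment of 50 and 500 per arm.

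**3. Effect of carry-forward on a rate.** Let m be the share missing at month 6 and q the share of those last recorded as non-smokers. Then

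rate under carry-forward = rate under missing-as-smoker + m × q.

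The added m × q is error to the extent that those people have relapsed. The illustrations take all of them as relapsed. The article does not give q, so it is varied. For m the planned dropout rates are used. Those rates leave out losses due to relapse, so total missingness could be higher.

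**4. Power formula** (two-sided 0.05, z = 1.96, n per arm, p̄ the mean of p₁ and p₂):

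power = Φ[(|p₂−p₁| − z·√(2p̄(1−p̄)/n)) / √((p₁(1−p₁)+p₂(1−p₂))/n)], plus the negligible or small opposite tail.

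This compares two proportions at month 6. It does not model the planned repeated ANOVA.

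**5. Same m and q in both arms**

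| Pilot | m | q | Rates | Risk ratio | Power |
|---|---|---|---|---|---|
| Public, n = 500 | – | 0 | 7% vs 14% | 2.00 | 0.952 |
| Public | 20% | 0.25 | 12% vs 19% | 1.58 | 0.865 |
| Public | 20% | 0.50 | 17% vs 24% | 1.41 | 0.784 |
| Public | 20% | 0.75 | 22% vs 29% | 1.32 | 0.719 |
| Clinical, n = 50 | – | 0 | 20% vs 50% | 2.50 | 0.894 |
| Clinical | 15% | 0.50 | 27.5% vs 57.5% | 2.09 | 0.870 |

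For the third row: 0.20 × 0.50 = 0.10 is added to each arm. The difference stays at 0.07, while the standard error under the alternative rises from 0.0193 to 0.0254.

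**6. Unequal missingness, no true effect** (public, 7% in both arms, 20% missing in one arm and 30% in the other)

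| q | Rates | Spurious difference | Chance of p<0.05 |
|---|---|---|---|
| 0.25 | 12% vs 14.5% | 2.5 points | 0.21 |
| 0.50 | 17% vs 22% | 5 points | 0.51 |
| 0.75 | 22% vs 29.5% | 7.5 points | 0.78 |

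The arm that loses more such participants looks better. Swapping the arms gives the same rejection rates with the sign reversed.

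**7. Unequal missingness, planned effect present** (clinical, q = 0.5). With 15% missing in control and 30% in intervention, 20% vs 50% becomes 27.5% vs 65%, a difference of 37.5 points. With 30% and 15% it becomes 35% vs 57.5%, a difference of 22.5 points, and power falls from 0.894 to 0.62.

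**The case against.** The best defence is that the specific rule overrides the general one. The failure rule addresses month-6 non-return directly, whereas the carry-forward sentence closes a paragraph mostly about secondary outcomes and software. On that reading carry-forward would serve only the other variables and the earlier visits. The reading is sensible, but the article does not state it, and the carry-forward sentence has no limit of scope. For the same reason, it cannot be said that carry-forward is the settled rule for month 6.

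Several further objections stand and limit the point:

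- **Scope.** The failure rule speaks of a consultation, which only the clinical pilot has. A reader might infer an outright contradiction in both pilots. In the public pilot there is ambiguity: the paragraph covers both dropout rates, yet its wording does not fit users who never attend.
- **Best state.** A reader might infer that carry-forward fixes people at their best status because abstinence can only be lost. Status is judged at each time point and quit attempts are recorded, so a smoker at day 60 can be abstinent at day 180. Carry-forward fixes the last status.
- **Direction.** A reader might infer that the bias favours the app. The article expects tailored messages to raise engagement; if that means fewer silent users, the bias would run against the intervention.
- **Missing-as-smoker is not neutral.** It too can bias the contrast when response differs by arm.

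**Conclusion.** The point holds as a conflict between two stated rules for the primary outcome. It is not a complaint about missing detail. It is clear-cut for clinical-pilot patients last recorded as non-smokers who miss month 6, and unresolved for the public pilot.

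Carry-forward overstates abstinence by the share of participants who are missing, were last recorded as non-smokers and have since relapsed. If that share is equal in both arms, the risk difference survives, while the risk ratio and power fall: modestly in the clinical pilot and more in the public pilot. If it is unequal, the contrast is biased towards the arm that loses more such participants. The 51% false-positive figure is correct arithmetic on assumed shares of 10% and 15%. It shows what could happen and does not predict the size or sign of the bias in this trial.

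A reader might also infer that the whole sample-size calculation rests on the failure rule. Only the argument for the 15% and 20% dropout rates does; the planned proportions cite no missing-data rule.

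**What to change.** In the Statistical analysis section, replace carry-forward for smoking status with one rule for both pilots: any randomised participant without a valid assessment at a time point is counted as a smoker at that time point. This matches the sample-size section at month 6, extends it explicitly to the earlier time points and to the public pilot, and fits the existing treatment of discordant tests. Confine carry-forward to other variables, or drop it.

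Because missing-as-smoker can itself bias the contrast, add one sensitivity analysis per pilot that varies the assumption separately by arm, for example multiple imputation or a tipping-point analysis.

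The cost is a sentence, a little more analysis and lower reported abstinence rates. Sample size is unaffected: under this rule the planned rates stand, with power 0.894 at 50 per arm and 0.952 at 500 per arm.
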